##### Sample Size Calculation

According to prior estimates provided by the CI(U)SSS, about 50 older adults may be targeted for participation per FMG per year. Considering that the on-site presence of FMG pharmacists is on average 2 to 3 days a week [11,12], it should be feasible to include approximately 40 older adults per FMG. By setting our intercluster correlation coefficient at 0.005 (conservative), the number of clusters (FMGs) at 5 intervention and 5 control FMGs, and at 40 older adults per FMG, we expect to be able to detect a difference of 1 medication per older adults between the beginning and the end of the intervention, between the 2 groups, with a power of 83%. Therefore, we have planned a 12-month inclusion period, corresponding to recruiting approximately 1 person per week per FMG. The inclusion date will be when the reference to the pharmacist was made. For control FMGs, we will consult electronic medical records and FMG health care professionals to identify all older adults who meet the inclusion criteria. Since there will be no reference to the pharmacist for these individuals, the inclusion date will be the date of identification by the FMG. For those receiving home care services, the inclusion date will be the first home visit following the start of the study.

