##### Outcomes Measures

The primary outcome measure is the change in the number of prescribed medications. Specifically, (1) the total number of prescribed medications and (2) the number of potentially inappropriate medications according to the Beers criteria [33] will be measured in the intervention and control groups. We will obtain data from patients’ medical records at the beginning (baseline) and 6 months after inclusion in the study.

We will assess several secondary outcome measures. First, a change in the treatment burden level will be measured with the 13-item MTBQ [26,27] in the intervention and control groups at baseline and 6 months follow-up. We will score each item as follows: 0 (not difficult/does not apply), 1 (a little difficult), 2 (quite difficult), 3 (very difficult), and 4 (extremely difficult). We will interpret the scores as suggested by the authors of the original MTBQ instrument: no burden (score 0), low burden (score <10), medium burden (score 10-22), and high burden (score ≥22) [26].

Second, we will measure the quality of life in the intervention and control groups at baseline and 6 months follow-up with the EQ-5D-5L [28]. The descriptive system comprises 5 dimensions: mobility, self-care, usual activities, pain/discomfort, and anxiety/depression. Each dimension has 5 levels: no problems, slight problems, moderate problems, severe problems, and extreme problems. Responses are coded as single-digit numbers expressing the severity level selected in each dimension [28]. The last study outcome is the satisfaction with the care received and access to care. To measure this outcome, the PESQ, validated in Quebec primary care settings, will be used [29]. We have adapted the questions with the author’s approval to consider not only the physician but the whole FMG team.

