### Data Analysis

In step 1, we will use an intention-to-treat approach to assess the GPS intervention’s effectiveness. The principal analysis will compare the difference (1) in the average number of medications per person between the unexposed and exposed groups according to the study period (baseline and 6 months) and (2) the average number of potentially inappropriate medications per person between the 2 groups, according to the study period, by mixed Poisson repeated measures regression. This type of analysis considers intra-FMG and intraindividual correlations. Contrasts will be built to determine if the average number of medications per person over time differs between the exposed and the unexposed group. Secondary results will be analyzed similarly to compare the MTBQ, PESQ, and EQ-5D-5L scores between the groups exposed and unexposed to the GPS intervention.

Medication data missing at measurement time periods after the initial data collection will be imputed using the last-observation-carried-forward method. Using this method, the potential benefits of the intervention should be underestimated. For participants lost to follow-up regarding the questionnaires, no measures will be imputed at follow-up, but sensitivity analyses may be used in which baseline questionnaires scores could be imputed for follow-up scores. We will perform all analyses with SAS statistical software (SAS Institute Inc).

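### Carrying baseline medication counts forward is not bound to underestimate benefit: with unequal missingness and a change in counts over time it can create or inflate it

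*Protocol article*

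**What the plan says.** In Outcomes Measures: "The primary outcome measure is the change in the number of prescribed medications". Both the total count and the count of potentially inappropriate medications are taken from medical records "at the beginning (baseline) and 6 months after inclusion in the study". There is no intermediate measurement.

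In Data Analysis, "we will use an intention-to-treat approach to assess the GPS intervention", and the group-by-period comparison is made "by mixed Poisson repeated measures regression". For missing values: "Medication data missing at measurement time periods after the initial data collection will be imputed using the last-observation-carried-forward method". The reason follows directly: "Using this method, the potential benefits of the intervention should be underestimated". No condition is attached to it.

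The questionnaires are handled differently. Their missing follow-up scores are left missing in the main analysis, and as an option "sensitivity analyses may be used in which baseline questionnaires scores could be imputed for follow-up scores".

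**The concern.** With a single follow-up time, last observation carried forward (LOCF) is baseline carried forward: every patient without a 6-month count is recorded as unchanged. Whether that works against the intervention depends on what the missing patients would have shown and on how many are missing in each group. The article presents the direction of bias as a property of the method, and it is not.

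Equal missingness cannot be taken for granted here. Groups are not randomised, and family medicine groups (FMGs) join at their convenience. Intervention patients enter by referral to the pharmacist, whereas controls are identified from records and by staff. Intervention pharmacists document a validated medication history and their actions for 6 months; no matching process is described for controls. By September 2022, 11 FMGs had agreed to implement the intervention and 2 to act as controls, so one control clinic's record-keeping could weigh heavily.

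What is at stake is how a positive primary result is read. Readers would be told that it is conservative when that has not been shown. LOCF also treats imputed values as if they had been observed.

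**Working it through.** **Inputs from the article.** Two measurement times; LOCF for missing medication counts; a design difference of 1 medication ("we expect to be able to detect a difference of 1 medication per older adults"); 5 + 5 FMGs of 40 patients; intracluster correlation 0.005; power 83%.

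**Inputs that are assumptions.** The missing fractions dI (intervention) and dC (control), and the mean 6-month change T that control patients would show (the drift). The article gives none of these. E is the true effect; a negative value means fewer medications in the intervention group, that is, benefit.

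**The plan's own figure.** The article states no figure for the size of this bias. The 83% power does not depend on it, and the standard deviation behind it is not given, so the figure is neither confirmed nor contradicted. Solving backwards: the design effect is 1 + 39 × 0.005 = 1.195 and the effective size is 200 / 1.195 = 167.4 per group. With a two-sided 5% level and a normal approximation, 83% power implies a standard deviation of about 3.14. It is used below only to set a scale.

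**Expected LOCF contrast.** If loss is unrelated to the count within each group, the expected difference in mean change on a linear scale is

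(1 - dI)(T + E) - (1 - dC)T = E(1 - dI) + T(dC - dI).

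The first term shrinks the effect, which is the authors' argument. The second has no fixed sign. It is zero if dI = dC or T = 0. It favours the intervention if counts rise and more intervention patients are missing, or if counts fall and more controls are missing.

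| True effect E | Drift T | dI | dC | Calculation | LOCF result |
|---|---|---|---|---|---|
| 0 | 0 | 0.3 | 0.1 | 0 | 0 |
| 0 | +0.5 | 0.3 | 0.1 | 0.35 - 0.45 | -0.10 (false benefit) |
| 0 | +1.0 | 0.3 | 0.1 | 0.7 - 0.9 | -0.20 (false benefit) |
| 0 | -1.0 | 0.1 | 0.3 | -0.9 + 0.7 | -0.20 (false benefit) |
| 0 | +1.0 | 0.1 | 0.3 | 0.9 - 0.7 | +0.20 (false harm) |
| -1 | any | 0.2 | 0.2 | -1 × 0.8 | -0.80 (shrunk) |
| -1 | 0 | 0.3 | 0.1 | -0.7 - 0 | -0.70 (shrunk) |
| -1 | +1.0 | 0.3 | 0.1 | 0 - 0.9 | -0.90 (shrunk) |
| -1 | +2.0 | 0.3 | 0.1 | 0.7 - 1.8 | -1.10 (inflated) |

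**How much drift inflates a real effect.** With E = -1, the result goes beyond -1 when T(dI - dC) > dI. At 30% v 10% that is 0.2T > 0.3, so T must exceed 1.5 medications in 6 months. Creating a benefit from nothing takes less: any rise will do at these missing fractions.

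**False-positive rate.** This was simulated with 20,000 trials per setting, 5 + 5 clusters of 40, intracluster correlation 0.005, an assumed standard deviation of change of 3.1, and a t test on cluster means with 8 degrees of freedom as a linear stand-in for the Poisson contrast. With no true effect and 30% v 10% missing, a significant benefit (nominal 2.5%) appeared in 2.3% of trials at zero drift, 4.7% at +0.5 and 8.6% at +1.0. With 20% missing in both groups and drift +1.0 it appeared in 2.5%.

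**The case against.** Several points on the other side stand.

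- **The sizes are assumed.** The article gives no dropout rate, no difference in dropout and no 6-month trend. A reader might infer that unequal dropout alone creates benefit. It does not: when loss is unrelated to outcome, a drift in the matching direction is needed as well. With equal missingness the authors' sentence is correct.
- **The outcome is abstracted from charts.** A patient who stops answering questionnaires need not lose a medication count, and the article treats the two kinds of missingness separately. Against that, 30% v 10% is a severe case, and the illustrated 0.1 to 0.2 medication is small beside the design difference of 1.
- **The arithmetic is linear.** The planned model is Poisson, normally with a log link, so the formula illustrates the mechanism and is not the exact bias of the planned contrast.
- **An analysis of observed data is not immune.** A reader might infer a much larger fault in LOCF by supposing that those lost would have gained 2 medications each. That makes loss depend on unobserved counts, and the preferred analysis is then biased too. With no true effect, 30% v 10% missing and an overall rise of 0.5 in both groups, observed changes average (0.5 - 0.6)/0.7 = -0.14 and (0.5 - 0.2)/0.9 = +0.33, a difference of about -0.48. LOCF gives -0.1 - 0.3 = -0.40. The case does not rank LOCF below the alternative; it argues for a delta analysis.
- **Other missing-data items are not faults.** A reader might extend the criticism to the questionnaires, to chart abstraction or to patients who die. Questionnaires are not imputed in the main analysis, charts are already the source, and the article does not say that values are carried past death. Further sensitivity analyses may stand in an analysis plan that is not shown.

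None of this makes the unconditional claim of conservatism true.

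**Conclusion.** The concern holds in a limited form. LOCF is the stated handling of missing primary-outcome data, and the direction of bias claimed for it is not a property of the method. It shrinks the effect when missingness is equal or counts do not drift. It can create or inflate benefit when missingness differs and counts move in the matching direction, or when loss is related to outcome; in the opposite configuration it works against the intervention. A reader might infer that LOCF generally favours the intervention here, or that the primary result would be invalid. The documents support neither, because the sign and size depend on dropout and drift that they do not give.

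The figures above rest on assumed missing fractions, an assumed drift, a linear scale and loss unrelated to outcome within each group. Because counts come from records, the actual bias may be small. Severity is moderate: the reasoning should be corrected and the primary handling changed, but nothing shows that the trial's conclusions would turn on it.

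**What to change.** 1. Make the primary analysis the planned mixed Poisson repeated-measures model, fitted by likelihood to all observed medication counts with no imputation. Patients with only a baseline count stay in the model, and the analysis is valid if data are missing at random. This matches the no-imputation rule already planned for the questionnaires.
2. Move LOCF to a sensitivity analysis. Beside it, add a delta analysis that shifts the assumed 6-month counts of missing patients by amounts that may differ between groups, since the missing-at-random analysis is also biased if loss depends on unobserved counts.
3. Delete the sentence saying that benefits should be underestimated.
4. Report the share of missing 6-month counts, with reasons, by group, so that readers can judge how much the choice matters.

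The cost is a change of wording, one extra sensitivity analysis and no new data. Removing the imputation step from the primary analysis saves some programming.

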### Ethics Approval

Ethical approval was obtained from the Ethics review board of the CISSS CA and CIUSSS NIM (project number: MP-23-2020-732; latest amendments approved in January 2022).

### Safety Consideration

The participant’s consent to participate in the study will be obtained in writing or verbally, recorded using an audio device. All participants will be able to withdraw from the study at any time without giving reasons. All patient data will be collected and recorded into REDCap, a secure and confidential data entry software. Nominal patient data will be entered into a data collection sheet and confidentially stored in an ongoing computer database of the research center (*CHU de Québec*).

## Results

All study materials (questionnaires, patients’ recruitment tools, and training documents) have been developed in collaboration with clinicians and patient partners. As of September 2022, 13 FMGs have agreed to participate in the GPS project (11 implementing the intervention and 2 as controls). We have yet to recruit more FMGs that will be part of the control group. Recruitment of older adults began in September 2021, when the project was launched. We had planned 12 months for the inclusion of eligible older adults. As of September 2022, a total of 100 participants had been enrolled and the follow-up was completed for 23 of them. Data collection will take approximately 18 months, and data analysis and synthesis of the results will take another 9 months. Knowledge transfer/mentoring sessions will be organized regularly during the implementation period (ten 1-hour meetings in each CI[U]SSS have been realized as of September 2022) and are also planned after the end of the GPS study (approximatively 6 months). These sessions are open to FMG pharmacists, physicians, mentors (physicians and pharmacists with geriatric expertise), and research team members and comprise short presentations of specific clinical interest, summaries of issues surrounding the study methods and procedures, as well as an occasion for an exchange between all these persons on clinical and research questions.

## Discussion

Our hypothesis is that the GPS intervention will improve pharmaceutical care for older adults undergoing cognitive assessment or with MNCDs and facilitate access to care. This research will add new knowledge on the impact of a systematic involvement of pharmacists in FMGs and their home care teams for older adults with MNCDs. In fact, despite growing recognition of the urgent need to address the “epidemic of polypharmacy in geriatric patients,” this study is one of the first to evaluate the impact of an interdisciplinary care model involving FMG pharmacists on the pharmacotherapy of older adults with MNCDs. It will also evaluate the processes required to implement the GPS intervention and develop tools, procedures, and guidelines that could be transposed to other care settings to improve care and its continuity for these patients.

This study received financing as a “living laboratory,” meaning that the proposed intervention will be adapted by the participating FMGs or home care teams and may thus vary slightly according to the different contexts of practice environments. This variability could influence the internal validity of the results, which is a possibility common in such strategies. Additionally, the COVID-19 pandemic has caused delays in deploying the project across the FMGs and brought some difficulties in patient recruitment. It might also be more challenging to recruit further FMGs because health care professionals must be willing to invest some time in implementing the intervention or for recruiting participants. Moreover, the characteristics of participants at risk or with a MNCD (eg, fatigue, memory loss, attention difficulties, anxiety, etc) may affect their level of understanding of their involvement in the project and possibly complicate data collection. Adjustments will be made in the methodology to account for the characteristics of the study population if necessary.

## Abbreviations

BPMH: best possible medication history
CA: Chaudière-Appalaches
CISSS: Centre intégré de santé et de services sociaux
CIUSSS: Centre intégré universitaire de santé et de services sociaux
FMG: family medicine group
MNCD: major neurocognitive disorder
MTBQ: Multimorbidity Treatment Burden Questionnaire
NIM: Nord-de-l’Ile-de-Montréal
PESQ: Physician Enabling Skill Questionnaire
